### Primary endpoint

The primary endpoint is the proportion of patients starting with ACT after detection of ctDNA in the post-surgery sample.

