### Sample size considerations

The primary endpoint is the proportion of ctDNA positive patients starting with ACT. However, 2-year RR in the ctDNA positive patients after surgery is an important secondary endpoint and the power calculation is performed for this secondary endpoint. We estimate that, similar to effectiveness in stage III CC patients, ACT in ctDNA-based high-risk stage II CC patients will lead to a 30% absolute reduction of recurrences within 2 years after surgery. In the observational trial 79% of patients with detectable ctDNA experienced disease recurrence within 2 years after resection [21].

With a power of 80% and an alpha of 0.05, 30 patients with detectable ctDNA need to be included in both arms. Assuming a prevalence of ctDNA after surgery of 5%, and adjustment for loss to follow-up and rejection of adjuvant therapy in the intervention arm of 10%, a total sample size of 1320 patients is calculated (660 in each arm). We expect few patients with detectable ctDNA in the intervention group to refuse ACT, because patients are selected upfront for being in a physical condition to receive ACT and the established prognostic value of detectable ctDNA is high.

We assume that cross-over from the control arm to the intervention arm will not occur, because only eligible patients randomly selected in the cohort and allocated to the intervention arm will be informed about the trial and have the opportunity for immediate analysis of ctDNA. Patients in the control group will not be informed about the trial or their ctDNA status.

We assume that 90% of patients in the intervention arm with detectable ctDNA will be treated with ACT. The proportion of patients starting with chemotherapy, the primary endpoint, can in that instance be determined with a margin of error (width of the 95% confidence interval) of 11%.

We expect to complete recruitment of patients within 2–3 years with more than 20 participating Dutch hospitals.

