This study has also potential limitations and challenges. The TwiCs design is potentially susceptible to low statistical power and internal validity biases. Levels of participant’s eligibility and consent should be substantial to achieve valid and reliable results, and measurements taken in the control group should be sufficient for adequate comparisons to be made [33]. Therefore the TwiCs design is not appropriate for every experimental intervention. In case of the MEDOCC-CrEATE study, we argue that eligibility and also consent will be substantial because of the high incidence of CC, the large cohort with high inclusion rates and the assumption that eligible patients in the intervention group are willing to accept ACT because of the very strong association of the presence of ctDNA with recurrent disease.

Another limitation is the small sample size for primary outcome analysis. Eventually only 30 patients in both arms of the trial are expected to have detectable ctDNA after surgery. Based on previous data, 80% relapses are expected within 2 years, and with a high event rate small numbers are sufficient [21].

We recommend a 6-month duration of ACT consisting of capecitabine and oxaliplatin (CAPOX) or fluorouracil, leucovorin and oxaliplatin (FOLFOX) for patients with detectable ctDNA after surgery. The first adjuvant CC trials investigating the combination of a fluoropyrimidine and oxaliplatin reported results for 6 month duration of ACT [34]. In 2018 the IDEA trial found a large reduction in toxicity for 3 months treatment compared to 6 months treatment. Although this trial could not confirm non-inferiority for 3 months treatment for all patients treated with CAPOX or FOLFOX in stage III CRC, the small difference limits clinical relevance. Besides, it did show non-inferiority of the shorter regimen in patients treated with CAPOX. Consequently, Dutch guidelines recommend 3 months of ACT for CC since 2019. However, among patients with highest risk of recurrence (T4, N2, or both) superiority of 6-month duration of therapy was found. Additional IDEA-FRANCE results, presented at the ESMO Congress 2019, showed the worst prognosis for ctDNA positive patients who only received 3 months of ACT [35]. Therefore in this study, we recommend 6-months ACT for patients with a very high risk of disease recurrence due to the presence of ctDNA after surgery.

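### The 11% precision quoted for the primary endpoint is a half-width, not the width of the 95% confidence interval, which is about 21 points

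*Protocol article*

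**What the plan says.** The Primary endpoint section of the protocol article defines the endpoint: "The primary endpoint is the proportion of patients starting with ACT after detection of ctDNA in the post-surgery sample". Sample size considerations repeats it with the denominator made explicit: "The primary endpoint is the proportion of ctDNA positive patients starting with ACT". That section bases the power calculation on 2-year recurrence rate instead, and from it obtains the requirement that "30 patients with detectable ctDNA need to be included in both arms".

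For the primary endpoint it gives one assumption and one precision figure. The assumption is: "We assume that 90% of patients in the intervention arm with detectable ctDNA will be treated with ACT" (ACT being adjuvant chemotherapy). The precision figure is that the proportion "can in that instance be determined with a margin of error (width of the 95% confidence interval) of 11" percent. No interval method is named, and the sentence does not give its denominator.

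Two denominators can be drawn from the article. The Discussion says "Eventually only 30 patients in both arms of the trial are expected to have detectable ctDNA after surgery", and Data analysis likewise compares 30 patients with 30, so this means 30 per arm. The inflated total ("a total sample size of 1320 patients is calculated (660 in each arm") combined with the prevalence assumption ("Assuming a prevalence of ctDNA after surgery of 5" percent) gives 660 × 0.05 = 33 in the intervention arm.

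**The concern.** A margin of error is ordinarily the half-width of a confidence interval; the width is the distance between its limits. The sentence treats the two as the same quantity and gives one number for both, so at most one label can be right.

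A reader who takes the parenthesis at its word expects limits 11 points apart, roughly 84.5% to 95.5% around 90%. A reader who takes the main term at its word expects roughly 79% to 101%. These say different things about how firmly the trial can establish willingness to accept ACT, which is its primary question. Since the power calculation concerns a secondary endpoint, this sentence is the only quantitative planning statement for the primary one.

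**Working it through.** **Inputs.** Uptake p = 0.90, 95% level, 30 ctDNA-positive intervention patients (all from Sample size considerations; the 30 is repeated in the Discussion). Alternative denominator: 660 × 0.05 = 33.

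**Step 1: reproduce the 11%.** Normal-approximation (Wald) half-width = 1.96 × √(p(1 − p)/n).

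- n = 30: 1.96 × √(0.09/30) = 0.107, which rounds to 11%.
- n = 33: 1.96 × √(0.09/33) = 0.102, which rounds to 10%.

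So the figure reproduces at n = 30, as a half-width.

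**Step 2: the full width.**

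- n = 30: 2 × 0.1074 = 0.215, from 79.3% to 100.7%.
- n = 33: 2 × 0.1024 = 0.205, from 79.8% to 100.2%.

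**Step 3: can any input in the article give a width of 11 points?** The n needed is 0.09 × (1.96/0.055)² = 114.3, so about 115 ctDNA-positive intervention patients. The Experimental arm section gives a prevalence range of 5–8%. At 8%, 660 × 0.08 is about 53 patients, and the width is 2 × 1.96 × √(0.09/53) = 0.16. Even at a 90% confidence level with n = 33 the width is 17.2 points. Nothing in the article yields 11.

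**Step 4: does plus or minus 11 points describe the uncertainty?** Two intervals that respect the 0–100% range:

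| Observed | Method | 95% limits | Width | 90% minus lower limit |
|---|---|---|---|---|
| 27/30 = 90% | Wilson | 74.4% to 96.5% | 22.2 points | 15.6 points |
| 27/30 = 90% | Clopper-Pearson | 73.5% to 97.9% | 24.4 points | 16.5 points |
| 30/33 = 90.9% | Wilson | 76.4% to 96.9% | 20.4 points | – |
| 30/33 = 90.9% | Clopper-Pearson | 75.7% to 98.1% | 22.4 points | – |

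At 27/30 the uncertainty is asymmetric: about 16 points downward, and 6.5 (Wilson) or 7.9 (Clopper-Pearson) upward. A symmetric 11 understates the downside, which is the side that matters for a claim about acceptance. With 33 patients, 90% is 29.7 patients, so no observed count equals it; the last two rows use the nearest, 30/33.

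**The case against.** The strongest defence is that the number is right and only its gloss is wrong: 11% is correct for a margin of error, and changing one word would remove the contradiction. That stands as far as it goes. The parenthesis is nonetheless an explicit definition and it is false; and once relabelled, the figure still implies an upper limit above 100% and a lower limit some 5 points too high.

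It is also fair to say that little hangs on the number. The 30 per arm and the 1320 come from the recurrence calculation, the article attaches no test or success threshold for the primary endpoint to the 11%, and the Discussion openly lists the small sample as a limitation. This stands and limits the weight of the point.

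Two stronger readings are tempting and should not be adopted:

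- **That the trial will analyse its primary endpoint with a Wald interval of poor coverage.** The article names no method. Wald is inferred only because it reproduces the 11%, and the choice for the final analysis may properly sit in an analysis plan that is not shown. The coverage argument is also sensitive to where one looks: with n = 30 the exact coverage of the Wald interval is 81% at p = 0.90 but 94% at p = 0.91. The overshoot past 100% is itself small, 0.7 point at n = 30 and 0.2 at n = 33.
- **That 30 is the wrong denominator.** Data analysis does describe the 30 intervention patients as having received ACT, which could suggest that 30 is the numerator. But Sample size considerations and the Discussion both give 30 as the number with detectable ctDNA, and the endpoint is already defined over ctDNA-positive patients. Using 30 rather than 33 also makes the stated precision slightly worse, not better.

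**Conclusion.** The sentence is wrong as written. On the article's own inputs, 11% is the half-width (10.7 points at n = 30); the 95% interval is 21.5 points wide at n = 30 and 20.5 at n = 33, about twice what the parenthesis says. Read instead as plus or minus 11 points, it understates the distance to the lower limit, which is about 16 points for 27/30.

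The label error rests only on the stated 90% uptake and on a denominator of 30 or 33; the widest prevalence given, 8%, does not rescue it. The downside figure rests in addition on using a Wilson or Clopper-Pearson interval.

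Severity is moderate. The error misdescribes the expected precision of the primary endpoint, but it does not touch the sample size, the conduct of the trial or any decision rule in the article.

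**What to change.** Replace the sentence with a correctly labelled interval and its denominator. For example: *With 30 ctDNA-positive patients in the intervention arm and 90% uptake (27/30), the 95% confidence interval would be about 74% to 97% (Wilson, 22 points wide)*, or, if the exact method is preferred, *about 73% to 98% (Clopper-Pearson, 24 points wide)*.

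If the sponsor prefers the 33 patients implied by 5% of 660, the sentence should give the count on which the limits rest: 30/33 = 90.9%, Wilson 76% to 97%, Clopper-Pearson 76% to 98%. These limits should not be presented as belonging to 90% uptake.

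The cost is one sentence. No additional patients and no change of design are needed. The stated precision becomes less favourable than a reader of the present text would expect.

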### Data analysis

Data will be analyzed according to the intention-to-treat principle for the primary endpoint and the secondary endpoint of 2-year RR in patients with detectable ctDNA after surgery. In this analysis we expect to compare 30 patients with detectable ctDNA who received ACT in the intervention arm with 30 patients with detectable ctDNA in the control arm, i.e. based on ctDNA analysis performed retrospectively, at least 3 months after surgery, and not disclosed to patients and treating physicians. The proportion of patients that experience a recurrence in both arms will be compared by means of a chi-square test. In addition, for other secondary endpoints and exploratory analyses we will analyze time-to-event outcomes in patients in both arms with detectable ctDNA after surgery. Differences in time-to-event outcomes will be analyzed by standard survival methods, e.g. Kaplan-Meier curves compared by log-rank tests. Cox’s proportional hazards models will be used for multivariable analysis.

Comparison of QoL of the ctDNA positive patients in both study arms will be done using repeated measurements methods and including ACT as factor. QoL will also be analyzed for the whole population in both arms of the study. Treatment differences at each QoL assessment time point will be compared by means of the Wilcoxon Rank Sum Test.

A lifetime horizon will be applied for the cost-effectiveness analysis, parametric survival functions will be used to extrapolate DFS and OS curves beyond 5 years.

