### Secondary endpoints

The most important secondary endpoint is 2-year RR in patients with detectable ctDNA in their blood, expressed as the proportion of patients that experience a recurrence within 2 years after surgery. Detection of recurrences (in months after surgery) will occur by standard follow-up investigations including 3–6 monthly blood sampling of tumor marker CEA and 6 monthly imaging with ultrasound liver or CT abdomen and when indicated by symptoms. Radiological and/or histopathological evidence is used to confirm the recurrence; the date of the said investigation is considered the date of recurrence.

Data about follow-up, recurrences and survival are routinely collected within PLCRC using the Netherlands Cancer Registry (NCR), managed by the Netherlands Comprehensive Cancer Organisation (IKNL) to provide insight in the characteristics and magnitude of cancer in the Netherlands [28].

Other secondary endpoints include 2-year RR in a per-protocol analysis, 5-year RR (intention-to-treat and per-protocol analysis), time to recurrence (TTR), 2- and 5-year disease free survival (DFS) rate, 5- and 7-year disease-related OS rate, 2- and 5-year RR in patients with undetectable ctDNA after surgery, quality of life (QoL) and cost-effectiveness of the ctDNA-guided strategy.

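### The sample size for 2-year recurrence counts refusal of ACT as attrition, so the stated 80% power does not belong to the stated intention-to-treat analysis

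*Protocol article*

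**What the plan says.** The Data analysis section fixes the principle: "Data will be analyzed according to the intention-to-treat principle for the primary endpoint and the secondary endpoint of 2-year RR in patients with detectable ctDNA". The next sentence, which refers to that same analysis, forecasts the comparison with controls: "we expect to compare 30 patients with detectable ctDNA who received ACT in the intervention arm with 30 patients with detectable ctDNA". The intervention side is thus described by treatment received, the control side by ctDNA status alone. A treated-only analysis already has its own place under Secondary endpoints: "Other secondary endpoints include 2-year RR in a per-protocol analysis".

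Sample size considerations takes the control rate from an earlier cohort ("In the observational trial 79% of patients with detectable ctDNA experienced disease recurrence within 2 years after resection") and attributes the effect to the drug treatment itself: "ACT in ctDNA-based high-risk stage II CC patients will lead to a 30% absolute reduction of recurrences within 2 years after surgery". It then states: "With a power of 80% and an alpha of 0.05, 30 patients with detectable ctDNA need to be included in both arms". The step from there to 1320 patients uses 5% ctDNA prevalence and an "adjustment for loss to follow-up and rejection of adjuvant therapy in the intervention arm of 10" percent. On uptake, the section says: "We assume that 90% of patients in the intervention arm with detectable ctDNA will be treated with ACT". Nowhere is the 30-point effect reduced for the patients who will not be treated.

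**The concern.** Refusal and loss to follow-up are different problems. A patient lost to follow-up has no outcome, and recruiting more patients makes up for that. A patient who refuses ACT still has an outcome, stays in the arm to which she was randomised, and pulls that arm's recurrence rate towards the control rate. Recruiting more patients does not restore the effect size; the planned difference itself has to be reduced.

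The protocol treats both as a head-count matter, and its description of the intervention set as treated patients fits that view. At stake is the power of the comparison for which the trial was sized. The Discussion ties implementation in practice to a significant and substantial difference in recurrence, so readers will take the 80% at face value.

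**Working it through.** **Inputs from Sample size considerations.** Control recurrence 0.79; effect of ACT 0.30, hence 0.49 if treated; power 80%; alpha 0.05 with sidedness not stated; 30 ctDNA-positive patients per arm; prevalence 5%; combined allowance 10%; ACT uptake 90%. The test, from Data analysis, is a chi-square test of two proportions.

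**Step 1: reproduce the plan's figures.** With p̄ the mean of the two rates and d their difference,

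n = [z_α √(2p̄(1−p̄)) + z_β √(p1(1−p1) + p2(1−p2))]² / d².

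For 0.79 versus 0.49, p̄ = 0.64 and the two square roots are 0.679 and 0.645.

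- One-sided: (1.645 × 0.679 + 0.842 × 0.645)² / 0.09 = 30.6, so 31 per arm. Power at 30 per arm is 79.3%.
- Two-sided: (1.960 × 0.679 + 0.842 × 0.645)² / 0.09 = 39.0, so 39 per arm. Power at 30 per arm is 68.6%.

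Only the one-sided version comes close to 30. The total follows exactly: 30/0.05 = 600; 600 × 1.10 = 660 per arm; 1320 in all. So the plan's numbers rest on the undiluted 30-point effect, with refusal inside the 10% inflation.

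**Step 2: the intention-to-treat contrast.** Assumption: refusers recur at the control rate (the documents give no rate for them). Then the intervention-arm rate is 0.9 × 0.49 + 0.1 × 0.79 = 0.52, and the difference is 0.79 − 0.52 = 0.27. The same 27 points follow as 0.9 × 0.30 if ACT lowers risk by 30 points in those who take it and being assigned to the intervention arm changes nothing in those who refuse.

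**Step 3: numbers available.** 660 × 0.05 = 33 ctDNA-positive patients per arm before any loss; 33 × 0.9 = 29.7, about 30, if the whole 10% is lost to follow-up.

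**Step 4: power for 0.79 versus 0.52.** Power = Φ{[d√n − z_α √(2p̄(1−p̄))] / √(p1(1−p1) + p2(1−p2))}, with p̄ = 0.655 and square roots 0.672 and 0.645. One-sided at n = 33: (0.27 × 5.745 − 1.645 × 0.672)/0.645 = 0.69, and Φ(0.69) = 75.5%. The other cells follow in the same way:

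| Per arm | One-sided, 30 points | One-sided, 27 points | Two-sided, 30 points | Two-sided, 27 points |
|---|---|---|---|---|
| 33 | 82.7% | 75.5% | 72.9% | 64.1% |
| 30 | 79.3% | 71.9% | 68.6% | 59.9% |

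Exact calculation for the chi-square test at 27 points gives 76.0% and 71.3% (critical value for one-sided 0.05) and 66.3% and 59.9% (two-sided).

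**Step 5: range for uptake, 33 per arm.** With 5% untreated the rate is 0.505 and power is 79.3% one-sided (68.6% two-sided). With 20% untreated the rate is 0.55 and power is 67.1% (54.7%).

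**Step 6: size for 80% power at 27 points.** 38 per arm one-sided, which is 38/0.05 × 2 = 1520 randomised before loss; 48 per arm two-sided, which is 1920.

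**The case against.** The best defence is that the sentence in Data analysis only forecasts counts. The principle is named just before it, the Abstract repeats it, and a per-protocol version is listed separately. The Discussion speaks of 30 patients per arm with detectable ctDNA and says nothing of treatment. The 11% margin for the primary endpoint also fits 30 positive patients: 1.96 × √(0.9 × 0.1/30) = 10.7%. And 30 are expected in the control arm too, where nobody is offered ACT, so the 30 may simply be the uninflated target restated. This stands as far as it goes: the agreement with 33 × 0.9 does not prove that the 30 were derived as treated patients. But if 30 are positive, 90% uptake gives 27 treated, not 30, so the sentence still needs correcting. The power argument does not depend on it in any case, because refusal is placed in the inflation explicitly.

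A reader might infer more: that a treated-only comparison is actually planned, and that it would be biased because treated patients must remain recurrence-free until ACT starts. The documents do not support this. The stated principle and the separate per-protocol endpoint point the other way, and with recurrence sought by 3–6-monthly CEA and 6-monthly imaging, few recurrences could be recorded so early.

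A reader might also say that the 10% is spent twice, since 10% refusal alone uses it up in the intervention arm. The protocol declares one combined allowance without a split, and follow-up comes through the national cancer registry, so loss may be small. That is why power is shown at both 33 and 30 per arm.

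**Conclusion.** The point holds and should be fixed. The wording of the comparison set conflicts with the declared principle, and the 80% power refers to an effect that an intention-to-treat analysis is not expected to show under the plan's own uptake assumption. On the plan's implicit one-sided basis, power is about 76% if no ctDNA-positive patient is lost and 72% if the full 10% are. That is about 4 to 7 points below the 79.3% that 30 per arm gives without dilution; the three extra patients per arm offset only part of the loss.

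The two-sided figures of 64% and 60% should not be laid wholly at this door. At 30 per arm, power falls from 79.3% to 68.6% through sidedness alone and from 68.6% to 59.9% through dilution, so just over half of that drop belongs to a different question.

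The result assumes that refusers gain nothing from being assigned to the intervention arm and that uptake is 90%; step 5 shows the sensitivity to uptake. It concerns a secondary endpoint, though the one used for sizing, and does not undermine the design.

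**What to change.** 1. In Data analysis, remove the qualifier that limits the intervention side to treated patients. Define the intention-to-treat set as all randomised patients with detectable ctDNA after surgery, whether or not they accept ACT: about 33 versus 33 expected before loss to follow-up. Keep treated-only patients for the per-protocol analysis already listed.
2. In Sample size considerations, state the powered difference as 27 points (79% versus 52%) with its actual power, give the assumption about refusers and a range for uptake, and use the 10% inflation for loss to follow-up only.

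This is a change of wording and of the stated power. It adds no patients, but the power will read less favourably. Restoring 80% would be a separate decision, at the numbers in step 6.

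Optionally, a complier-average estimate (intention-to-treat risk difference divided by ACT uptake) could supplement the per-protocol analysis; it need not replace it. It requires that assignment affects recurrence only through ACT. That should be stated and is open to dispute here, because refusers know their ctDNA result and controls do not.

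### The 2-year recurrence comparison is labelled intention-to-treat but described as ACT recipients against ctDNA-positive controls; the population should be fixed as allocated and the power restated for refusal

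*Protocol article*

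**What the plan says.** Data analysis opens with the rule: "Data will be analyzed according to the intention-to-treat principle for the primary endpoint and the secondary endpoint of 2-year RR", the latter in patients with detectable ctDNA after surgery. The next sentence, referring to that same analysis, says the investigators expect to "compare 30 patients with detectable ctDNA who received ACT in the intervention arm with 30 patients with detectable ctDNA in the control arm". The control group carries no condition beyond detectable ctDNA.

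The per-protocol version is a separate item under Secondary endpoints: "Other secondary endpoints include 2-year RR in a per-protocol analysis". The sentence on ACT recipients therefore belongs to the main comparison.

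Non-starters are expected. The Experimental arm section leaves acceptance of ACT to the patient. Sample size considerations assumes that 90% of ctDNA-positive intervention patients are treated, and makes one 10% allowance covering loss to follow-up and rejection of ACT together. The same section sets the target: "With a power of 80% and an alpha of 0.05, 30 patients with detectable ctDNA need to be included in both arms". The Discussion repeats the figure: "Eventually only 30 patients in both arms of the trial are expected to have detectable ctDNA after surgery".

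**The concern.** Under ITT, a ctDNA-positive patient who declines ACT stays in the intervention arm. Under the sentence that follows, that patient is not among those compared. Both cannot hold, and an analyst could cite either.

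The comparison is the main secondary endpoint and the one on which the trial is sized. The Conclusion ties implementation in practice to a significant and substantial difference in recurrence. Randomizing before ctDNA is measured is the design's main protection, and conditioning one arm on a later event gives part of it up. Recurrence is counted from surgery while ACT may start up to 12 weeks later, so a patient whose disease recurred before starting could be lost from the intervention arm only. Uptake is itself the primary endpoint, so the size of the discrepancy depends on a quantity that the trial is set up to measure.

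**Working it through.** **Inputs, from Sample size considerations.** Control recurrence: "79% of patients with detectable ctDNA experienced disease recurrence within 2 years after resection". Effect: ACT "will lead to a 30% absolute reduction of recurrences within 2 years after surgery", giving 79% − 30 = 49% in treated patients. Uptake is 90%, ctDNA prevalence 5%, and there are 660 patients per arm. Whether alpha of 0.05 is one- or two-sided is not stated.

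**The plan's own figures.** The formula is n per arm = [z_α √(2p̄(1−p̄)) + z_β √(p₁(1−p₁)+p₂(1−p₂))]² / (p₁−p₂)², with p₁ = 0.79, p₂ = 0.49, p̄ = 0.64.
- One-sided: (1.645 × 0.679 + 0.842 × 0.645)² / 0.09 = 31, close to the stated 30.
- Two-sided: (1.960 × 0.679 + 0.842 × 0.645)² / 0.09 = 39.
- Total: 30 / 0.05 = 600; × 1.10 = 660 per arm; × 2 = 1320, as stated.

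The 30 thus reproduces only with a one-sided alpha, so both versions are given below.

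**Described contrast against ITT.** Let u be uptake, r the recurrence rate in non-starters and s the rate in treated starters. The described contrast is 79% − s. The ITT contrast is 79% − [u·s + (1−u)·r]. The excess of the first over the second is (1−u)(r − s).

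Assume r = 79%, so s = 49%:

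| Uptake | ITT intervention rate | ITT difference | Described contrast |
|---|---|---|---|
| 90% | 0.9 × 49 + 0.1 × 79 = 52% | 27 | 30 |
| 80% | 0.8 × 49 + 0.2 × 79 = 55% | 24 | 30 |
| 70% | 0.7 × 49 + 0.3 × 79 = 58% | 21 | 30 |

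Now vary r at 90% uptake, keeping overall untreated recurrence at 79%. Untreated starters then recur at (0.79 − 0.1r)/0.9.

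| Assumed r | Described contrast, 30-point effect | ITT, 30-point effect | Described contrast, no effect |
|---|---|---|---|
| 60% | 27.9 | 27 | −2.1 |
| 79% | 30.0 | 27 | 0 |
| 100% | 32.3 | 27 | +2.3 |

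With a 30-point effect in starters, the described contrast exceeds ITT unless r is below about 52% (solving r = (0.79 − 0.1r)/0.9 − 0.30 gives r = 0.52).

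**Power.** Power = Φ{[(p₁−p₂)√n − z_α √(2p̄(1−p̄))] / √(p₁(1−p₁)+p₂(1−p₂))}. For 79% against 52%, p̄ = 0.655 and the two roots are 0.672 and 0.645. At n = 33 two-sided: (0.27 × 5.745 − 1.960 × 0.672) / 0.645 = 0.36, so power is 64%.

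| Per arm | Alpha | 79% v 49% | 79% v 52% |
|---|---|---|---|
| 30 | one-sided | 79% | 72% |
| 30 | two-sided | 69% | 60% |
| 33 | one-sided | 83% | 76% |
| 33 | two-sided | 73% | 64% |

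Here 33 = 660 × 5%, before any loss to follow-up. For 80% power at 27 points, 38 per arm are needed one-sided or 48 two-sided.

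**The case against.** The strongest reply is that this is loose drafting. The sentence forecasts numbers and states no exclusion rule. The Abstract says the data will be analyzed by intention to treat, the endpoint is defined in patients with detectable ctDNA, and the per-protocol version is listed apart. This stands: the documents do not show that the sponsor means to drop non-starters, only that one sentence describes a population that the rule before it does not allow.

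A reader might infer that the arithmetic proves the starters-only reading, since 660 × 5% = 33 and 33 × 0.9 = 29.7. It does not:
- The same sentence gives 30 controls, who cannot refuse ACT.
- The 10% pools loss to follow-up with refusal and enlarges both arms alike.
- The stated 11% margin for the primary endpoint fits 30 as all ctDNA-positive intervention patients: 1.96√(0.9 × 0.1/30) = 10.7%, against 10.2% at n = 33. At n = 27 it is 11.3%, which also rounds to 11%, so this is only supportive.

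For the same reasons the 30 in the Discussion need not be an error; it matches the target in Sample size considerations.

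A reader might also infer that the described comparison must create benefit where there is none. That needs non-starters to have a worse prognosis than other ctDNA-positive patients, on which the document is silent. At r = 79% the spurious difference is zero, and at 60% it runs against ACT. Much of the gap between 30 and 27 points is the ordinary difference between an effect in starters and an effect by allocation.

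Finally, the sponsor could say that the 30 points were meant net of refusal. But the text presents them as the effect of ACT and allows for rejection by adding patients.

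**Conclusion.** The contradiction is real, sits on the powered comparison and is not resolved elsewhere in the article. If the sentence on ACT recipients governed, the contrast would exceed the ITT difference by 3 points at 90% uptake and 6 at 80%, assuming a 30-point effect in starters and non-starters recurring at 79%. The direction under no true effect cannot be stated from the document.

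If the ITT rule governs, as it should, the difference to plan for is 0.9 × 30 = 27 points, provided the 30 points are the effect in patients who start ACT and non-starters gain nothing. Adding 10% to the sample size replaces lost patients but does not restore the lost difference. The stated 80% power is then not met at 30 or 33 per arm under either sidedness. Dilution alone costs about 7 to 9 percentage points of power; the rest of the two-sided shortfall comes from the sidedness of alpha.

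**What to change.** In Data analysis, delete *who received ACT* and state that all patients with detectable ctDNA are compared by allocated arm, whether or not ACT was started. Keep any starters-only contrast for the per-protocol endpoint already listed. Leave the 30 in the Discussion as it is, as the evaluable target from Sample size considerations.

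In Sample size considerations, state that refusal reduces the expected ITT difference to about 27 points at 90% uptake, state whether alpha is one- or two-sided, and give the resulting power at 30 and 33 per arm.

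The wording change costs a sentence, removes no data, and should be made before outcomes by arm are known. The real cost is acknowledging power below 80%, or enlarging the trial. At 5% prevalence, 38 per arm means 38/0.05 = 760 randomized per arm and 48 means 960, in each case before loss to follow-up, against 660 now.
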